### Who will take informed consent?

Fieldworkers will provide all potential participants in the study with a consent form to read. The document will contain multiple diagrams and illustrations to explain the key concepts of the project. For illiterate participants, the fieldworkers will read the consent form in the native spoken language of the participants, as necessary. The consent form will outline the scope, purpose, and procedures of the study as well as the risks and benefits of study participation. The fieldworkers will answer any questions before asking for consent. If the potential participant meets the inclusion criteria (and the other members of the household do not meet the exclusion criteria) and wishes to participate, she or he will be asked to sign or thumbprint the consent form; the fieldworker will then countersign. If the participant is illiterate, a witness will sign in addition to the participant’s fingerprint. One signed consent form remains with the participant; a second signed consent form is retained by the study team. All study subjects will be informed that they may withdraw consent to participate in the trial at any point during the study.

### Additional consent provisions for collection and use of participant data and biological specimens

Participants will be informed that data collected from the trial may be used in ancillary studies or secondary analyses. As noted above, blood and urine will be obtained during the screening process to exclude those with preexisting renal dysfunction.

## Interventions

### Explanation for the choice of comparators

Our three study arms were chosen to determine (1) If a community health worker-administered intervention can be effectively used to disseminate LSSS, and (2) If such a program can lead to measurable blood pressure reduction. Thus, the control arm involves no intervention, while one intervention arm involves a community health worker-led education/counseling program and the other intervention arm involves community health worker-led education/counseling as well as free provision of LSSS.

### Intervention description

Basic Information/Education Intervention Arm: Community health workers will provide basic information and education on (i) the health consequences of high blood pressure and excessive salt consumption, (ii) feedback to the participant on the likely quantity of salt s/he consumes (estimated using a questionnaire), and (iii) advice on reducing salt consumption (Supplementary Material 1). This arm will allow for isolating the treatment effect of CHW-delivered participant education/information about hypertension and salt consumption alone.Information plus home delivery of free low-sodium salt intervention arm: in addition to the information intervention from arm 2, each household will be given a parcel (of approximately 1–2 kg) of low-sodium salt (Supplementary Material 2) on a monthly basis for free during community health worker household visits. This arm will serve to isolate the treatment effect of low-sodium salt itself.

### Criteria for discontinuing or modifying allocated interventions

The intervention arm involving free provision of LSSS product will be discontinued if a participant develops high blood potassium levels (hyperkalemia) or ends up meeting the exclusion criteria (i.e., develops kidney disease or is prescribed potassium supplements or potassium-elevating medications by their healthcare provider) at any point during the study. Any and all patients may discontinue participation in the trial at any time of their own volition.

### Strategies to improve adherence to interventions

As the present trial is testing the effectiveness of the delivery mechanism for LSSS, no specific strategies to improve adherence to the product will be undertaken for the purposes of encouraging adherence. All participants randomized to the free LSSS arm, however, will be asked not to share the product with other households to avoid cross-contamination. To monitor for compliance, intervention arm community health workers will measure any unused LSSS at each monthly visit.

### Relevant concomitant care permitted or prohibited during the trial

All participants will be encouraged to continue usual health care during the span of the trial. No changes should be made in their routine healthcare screening or therapy—rather, any participants found to have developed exclusion criteria medical conditions during the study will be removed from the free LSSS intervention arm.

### Provisions for post-trial care

The existing literature suggests that low-sodium salt substitutes provide beneficial effects at best and a neutral (or null) effect at worst. The product is already commercially available for purchase over the counter in other nearby countries and is used in many nations as a nutritional supplement without the requirement of physician or healthcare provider supervision.

### Outcomes

The primary outcome variable of our study is systolic blood pressure (SBP) as a continuous variable.

Secondary outcome variables will include:Diastolic blood pressure (DBP)Hypertension (defined as a systolic blood pressure ≥ 140 mm Hg or diastolic blood pressure ≥ 90 mm Hg or reporting to be taking antihypertensive medication)Systolic blood pressure among adults who had hypertension at the time of the baseline surveyDiastolic blood pressure among adults who had hypertension at the time of the baseline surveyHypertension control (defined as a systolic blood pressure < 140 mm Hg and a diastolic blood pressure < 90 mm Hg) among adults who had hypertension at the time of the baseline surveySelf-reported sodium intake (as estimated using typical daily dietary recall of both added salt and processed food/high salt food products)Self-reported low-sodium salt intake (as estimated using typical daily, 1-week, and 1-month recall)

### Participant timeline

The time schedule of enrolment, interventions, assessments, and visits for participants is provided via the schematic diagram below. There are no washout or crossover periods in this study.

**Table Taba:** 

	**Study period**								
	**Enrolment**	**Allocation**		**Post-allocation (in months)**					**Close-out**
**Timepoint**	*** − t***_***1***_	**0**	***t***_***1***_	***t***_***2***_	***t***_***3***_	***t***_***4***_	***t***_***5***_	***t***_***6***_	***t***_***7***_
**Enrolment:**									
**Eligibility screen**	60 days								
**Informed consent**	5 days								
***Baseline survey***	15 days								
**Allocation**		5 days							
**Interventions:**									
***Control group***									
***Education/information arm***			X	X	X	X	X	X	
***Free LSSS arm***			X	X	X	X	X	X	
**Assessments:**									
***Baseline survey***	X	X							
***Endline survey***									X
***LSSS interim use measurement***			X	X	X	X	X	X	X

## Sample size

Assuming a Type I error rate of 0.05 and a desired power of 0.80 for our study, we hypothesize an intervention effect of 2.0 mm of mercury (mm Hg) of systolic blood pressure reduction with standard deviation of 20.0 mm Hg. These values were extrapolated from prior RCTs of low-sodium salt interventions in LMICs, whose effect sizes have varied from 1.1 to 10 mm Hg (with variance around the order of 20–30 mm Hg) with most studies finding effect sizes of over 3.0 mm Hg in blood pressure reduction [30–37]. Uptake of the intervention in these studies ranged from 74.3 to 94.1%.

Assuming an analysis of simple difference of outcome, a conservative intra-cluster coefficient (ICC) of 0.25 (and an expected cluster membership of five adults per cluster), we estimated an average of 33 clusters would be necessary per study arm to detect an effect size of our proposed magnitude. This would suggest that a total enrollment of 660 study subjects would be needed for our study.

Below, a table (generated from the National Institutes of Health Sample Size Calculator for GRTs [group- or cluster-randomized trials]) noting the absolute detectable difference (in millimeters of mercury) for a range of cluster sizes by cluster numbers is presented:
[figure not shown]

Of note, we will be obtaining blood pressure measurements at baseline. Thus, having the correlation between baseline and endline BP will provide additional power over this very conservative estimate.

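### The stated inputs do not give 33 clusters per arm: with an SD of 20 mm Hg the planned trial has about 15% power for 2.0 mm Hg (18% to 33% after baseline adjustment), not 80%

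*Protocol article*

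**What the plan says.** The Sample size section of the protocol article sets "a desired power of 0.80 for our study" at a type I error rate of 0.05 and states: "we hypothesize an intervention effect of 2.0 mm of mercury (mm Hg) of systolic blood pressure reduction with standard deviation of 20.0 mm Hg". The calculation is for an unadjusted difference in outcome, with an ICC of 0.25 and five adults per cluster. It concludes: "we estimated an average of 33 clusters would be necessary per study arm to detect an effect size of our proposed magnitude", and gives a total enrolment of 660.

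The same paragraph describes the spread in earlier trials as "with variance around the order of 20–30 mm Hg". The section ends by noting that baseline blood pressure will also be measured and that its correlation with endline "will provide additional power over this very conservative estimate".

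The Recruitment section then fixes 206 participants per arm (618 in total) in 309 households. Eligibility criteria invites one man and one woman per household. The Statistical methods section adjusts the primary model for baseline blood pressure.

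**The concern.** An SD of 20 mm Hg against a target of 2.0 mm Hg is a standardised difference of 0.1. Even without clustering, that needs more than 1,500 people per arm. A requirement of 33 clusters of five, or 165 people per arm before allowance for uptake, cannot follow from it.

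Systolic pressure is the primary outcome, and this calculation is its only power justification. Readers are told that the trial has 80% power for 2.0 mm Hg and that this is a cautious figure. If the true power is a fraction of that, a non-significant result is the most likely outcome even when the target effect is real. It could then be misread as evidence against education or salt-substitute delivery by community health workers. The Dissemination plans include a policy brief to the Ministry of Health, so such a misreading could have practical consequences.

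**Working it through.** **Inputs (Sample size section).** Difference 2.0 mm Hg; SD 20, so variance 400; ICC 0.25; m = 5 adults per cluster; alpha 0.05, taken as two-sided because the sidedness is not stated; power 0.80; no baseline adjustment.

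**Formula.** Design effect DE = 1 + (m − 1) × ICC. With g clusters per arm, SE = √(2 × variance × DE / (g × m)). The smallest adequate g satisfies 2.0 / SE ≥ t(0.975) + t(0.80), on 2(g − 1) degrees of freedom.

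**1. The protocol's figure from its stated inputs.** DE = 1 + 4 × 0.25 = 2.0. Without clustering, 1,570 people per arm are needed. With clustering, 1,570 × 2.0 = 3,140 per arm, and 3,140 / 5 = 628 clusters (normal approximation) or 629 (t). A one-sided test would need 495 or 496. None of these is near 33; 629 / 33 is about 19.

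**2. The protocol's figure with 20 as the variance.** SD = √20 = 4.47. At g = 33, SE = √(2 × 20 × 2.0 / 165) = 0.696. The t quantiles on 64 degrees of freedom sum to 1.998 + 0.847 = 2.845, so the detectable difference is 2.845 × 0.696 = 1.98 mm Hg and power is 80.8%. At g = 32 power is 79.5%. The answer is therefore exactly 33 (32 by the normal approximation). The enrolment total follows as well: 33 × 5 × 3 = 495, and 495 / 0.75 (the uptake figure in Recruitment) = 660.

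**3. Power of 33 clusters of five at SD 20.** SE = √(2 × 400 × 2.0 / 165) = 3.11; power for 2.0 mm Hg is about 10%.

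**4. Power of the design actually fixed.** 309 / 3 = 103 households per arm, two adults each, 206 per arm. DE = 1 + 1 × 0.25 = 1.25. SE = 20 × √(2 × 1.25 / 206) = 2.20. On 204 degrees of freedom, power for 2.0 mm Hg is 14.7%. The difference detectable with 80% power is (1.972 + 0.843) × 2.203 = 6.2 mm Hg.

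**5. Adding baseline adjustment.** The protocol gives no baseline-endline correlation r, so a range is assumed. SE is multiplied by √(1 − r²), which takes the ICC of the adjusted outcome to be unchanged.

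| Assumed r | SE | Power for 2.0 mm Hg | Detectable difference at 80% power | 95% CI half-width |
|---|---|---|---|---|
| 0 (unadjusted) | 2.20 | 15% | 6.2 mm Hg | 4.3 mm Hg |
| 0.5 | 1.91 | 18% | 5.4 mm Hg | 3.8 mm Hg |
| 0.7 | 1.57 | 24% | 4.4 mm Hg | 3.1 mm Hg |
| 0.8 | 1.32 | 33% | 3.7 mm Hg | 2.6 mm Hg |

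Reaching 80% would need a correlation of about 0.95.

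**6. Sensitivity to the other inputs.** Moving the ICC from 0 to 0.5 changes unadjusted power only from 17% to 13%. An assumed SD of 15 with r = 0.7 gives 39%. Unadjusted, the design reaches 80% power only if the SD is about 6.4 mm Hg. These figures assume that all 206 participants per arm provide endline data and that the full 2.0 mm Hg effect is realised.

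**The case against.** Five points can be made for the plan.

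- **The cause is inferred.** The calculator table is not visible in the text reviewed, and the match to 33 holds for the t-based calculation only. The word variance in "with variance around the order of 20–30 mm Hg" carries mm Hg units and could be loose wording for an SD. This stands as a caution about mechanism. The mismatch between the printed inputs and the printed result does not depend on it.
- **The primary model adjusts for baseline, so 15% is not the power of the planned analysis.** This is correct. The 15% answers the protocol's own unadjusted calculation; 18% to 33% is the fairer range for the analysis planned. Neither is close to 80%.
- **Ignoring the baseline correlation is conservative in direction.** That is true as far as it goes. The remark fails because the calculation it leans on is wrong, so it is a consequence of the main error and not a second one.
- **Larger effects are plausible.** The protocol says that most earlier trials found more than 3.0 mm Hg. At r = 0.7 the design has about 48% power for 3 mm Hg and about 89% for 5 mm Hg. The trial is therefore not uninformative, but the effect it claims to be powered for is 2.0 mm Hg.
- **Perhaps a variance really was meant.** Then the plan rests on a between-person SD of about 4.5 mm Hg for systolic pressure, which appears nowhere and has no support in the text. The section would still need correcting.

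Nothing in the protocol says that a null result will be read as absence of effect. That risk is a reasonable inference from the stated power, not something the document plans.

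**Conclusion.** The concern holds. The inputs printed in the Sample size section require about 629 clusters per arm, not 33, and entering 20 as the variance is the very likely explanation. For 103 households of two adults per arm, power for 2.0 mm Hg is about 15% on the protocol's unadjusted basis and 18% to 33% with baseline adjustment at assumed correlations of 0.5 to 0.8. The difference detectable with 80% power is 6.2 mm Hg unadjusted and 5.4 to 3.7 mm Hg adjusted.

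These results rest on SD 20 and ICC 0.25 as stated, a two-sided test and complete follow-up. The conclusion is insensitive to the ICC, to one-sided testing in the original calculation and to a moderately smaller SD. No other section repairs the figure. Because it is the sole power statement for the primary outcome, it has to be corrected.

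**What to change.** In the Sample size section:

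1. Redo the calculation with a variance of 400 for the design being run: 103 households of two adults per arm, analysed with baseline adjustment under a stated and justified correlation.
2. Replace the claim of 80% power for 2.0 mm Hg with the actual power and detectable difference: 15% and 6.2 mm Hg unadjusted; 18% to 33% and 5.4 to 3.7 mm Hg for correlations of 0.5 to 0.8.
3. Remove the description of the estimate as conservative, and use the terms variance and SD consistently.
4. State that a non-significant result will not be taken to exclude a 2 mm Hg effect. The expected 95% CI half-width is about 4.3 mm Hg unadjusted and 3.8 to 2.6 mm Hg over the same correlations.
5. If an SD of about 4.5 mm Hg was intended, say so and give the evidence for it.

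The cost is the rewriting of one section and a less favourable stated power. Enrolment, outcomes and analysis need not change, and the correction can be made at any stage of recruitment.

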### Recruitment

Given concerns for lower uptake among study participants randomized to the education only arm, we decided to build a conservative estimate approximated from the lowest value of uptake in the literature of free salt substitute of 75% [31, 38]. This would support the selection of a final sample size of 206 participants per study arm, leading to a total study recruitment requirement of 618 subjects. This is well within the 2,181 subjects currently registered within the BRAC cohort described above.

We shall recruit study households in the following stages: (a) the eligible households in the sampling frame will be listed against the inclusion criteria, i.e., households without any diagnosed case of chronic kidney disease (CKD), nephrotic syndrome, or hyperkalemia, no history of current intake of potassium supplement or potassium-elevating medications, and households consisting of at least two adults (aged ≥ 18 years) willing to participate in the trial; (b) from the eligible households, we shall choose a systematic random sample (with an interval of five houses) to create buffers among study households to reduce the chances of spill-over; (c) the systematic random sample of 309 households will be further inflated by the current CKD prevalence of 17.3% in Bangladesh; the resulting 362 households will then undergo the randomization process [39]. We will plan to exclude the households with CKD or nephrotic syndrome cases; to ensure this, we will perform serum creatinine tests among the adults and urine dipstick tests among those under 18 years of age with the exclusion criteria previously enumerated.

The aforementioned recruitment areas of Uttor Basupara, Basupara, and Mondolpara are adjacent to one another and are further divided into six regions. As homes within these regions are not evenly clustered in an area (and do not adhere to a geographic grid with convenient central points of interest), we will designate one end of the area as the starting point. The field workers will use a random number generator to select the first household, then move on to enrolling homes sequentially, maintaining a gap of five households between enrolled homes. This process will be continued until the end of an area is reached.

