### Eligibility criteria

One male and one female adult (age ≥ 18 years) in each study household will be invited to participate. The exclusion criteria are subjects known to have high serum potassium levels, are taking medications known to potentially induce hyperkalemia (potassium-sparing diuretics, Angiotensin-converting enzyme (ACE) inhibitors, Angiotensin II receptor blockers, digoxin), are already taking potassium supplements, or those who have known kidney disease at baseline. Additionally, all adults residing in the selected households initially screened for intervention will undergo serum creatinine testing, with those with estimated glomerular filtrate rate (eGFR) values < 60 ml/min/body surface area excluded from the intervention but kept in the intervention group by intention-to-treat principles to avoid breaking of randomization. Although minors will not be involved in the study, to avoid spillover injury to children in the intervention households, all members of intervention households under the age of 18 will also undergo urine dipstick testing. If proteinuria (as +  + protein on urinalysis) is detected on two separate tests spaced three days apart, the household will be excluded from receiving the LSSS intervention (but followed in the intervention arm to avoid breaking randomization).

Lastly, potential participants (but not households) will be excluded if they have (1) a terminal illness, (2) are substantially mentally disabled (and thus unable to give consent), or (3) are bedridden.

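### The sample-size figures (33 clusters, 660, 618, 362) do not form one valid calculation, and they assume five adults per household where two are enrolled

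*Protocol article*

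**What the plan says.** **Sample size section.** The error rates are set out as "Assuming a Type I error rate of 0.05 and a desired power of 0.80 for our study", with an "intervention effect of 2.0 mm of mercury (mm Hg) of systolic blood pressure reduction with standard deviation of 20.0 mm Hg". The spread in earlier trials is described differently, "with variance around the order of 20–30 mm Hg". The ICC is 0.25, with "an expected cluster membership of five adults per cluster". From this the section obtains 33 clusters per arm and concludes: "This would suggest that a total enrollment of 660 study subjects would be needed for our study". It reports uptake of 74.3 to 94.1% in the trials from which the planning values were extrapolated.

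**Recruitment section.** This then introduces an uptake allowance based on "the lowest value of uptake in the literature of free salt substitute of 75"% and arrives at "a final sample size of 206 participants per study arm, leading to a total study recruitment requirement of 618 subjects". The 309 households are next increased for a CKD prevalence of 17.3%, giving 362 households to randomise.

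**Trial design and Eligibility criteria sections.** The household is the randomised unit, and one man and one woman "in each study household will be invited to participate". This agrees with 618/309 = 2 adults per cluster.

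**The concern.** The two sections should be consecutive steps of one calculation, but they do not connect. The stated requirement falls when an allowance for poor uptake is added. The first total does not equal clusters × cluster size × arms. The cluster size in the calculation is not the one the trial enrols.

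What is at stake is the meaning of the 80% power. The number recruited is 618 adults in 309 households, and no step in the text attaches 80% power to that design. If the result is null, a reader cannot tell from the plan what size of effect the trial could have detected.

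**Working it through.** **Inputs.** From Sample size: alpha 0.05, power 0.80, effect 2.0 mm Hg, SD 20.0, ICC 0.25, five adults per cluster, 33 clusters per arm, 660 in total. From Recruitment: 75% uptake, 206 per arm, 618 in total, 309 households, CKD 17.3%, 362 households. From Eligibility criteria: two adults per household. Sidedness is not stated; two-sided is assumed.

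**Step 1: the 660.**
- 33 × 5 = 165 per arm, and 165 × 3 = 495, not 660.
- 495/0.75 = 660, but 4 × 165 = 660 as well, so the origin cannot be proved.
- Either way, 660 is not the three-arm figure before any uptake allowance, which is how it is presented.

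**Step 2: the 206.**
- Dividing by uptake: 165/0.75 = 220 per arm, 660 in total.
- Adding the 25% shortfall: 165 × 1.25 = 206.25, hence 206 per arm and 618 in total.
- The stated figure matches the second form, n × (1 + d), where the correct form is n/(1 − d). It is 6.4% below 220.

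**Step 3: the 362.**
- Stated: 309 × 1.173 = 362.5, given as 362.
- Correct: 309/(1 − 0.173) = 309/0.827 = 373.6, so 374.
- The same slip appears twice, which supports the reading in step 2.

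**Step 4: the cluster size.** Design effect = 1 + (m − 1) × ICC.
- m = 5: 1 + 4 × 0.25 = 2.0.
- m = 2: 1 + 1 × 0.25 = 1.25.

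At a fixed number of adults, the enrolled design is the more efficient one.

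**Step 5: the 33 clusters.** Adults per arm = 2 × SD² × (1.960 + 0.842)² / effect² × design effect.
- SD 20: 2 × 400 × 7.849/4 = 1,570; × 2.0 = 3,140 adults; /5 = 628 clusters per arm (629 with t quantiles). One-sided: 495 to 496.
- 20 read as the variance (SD 4.47): 2 × 20 × 7.849/4 = 78.5; × 2.0 = 157; /5 = 31.4, so 32 clusters. With t quantiles on 2(g − 1) degrees of freedom the result is 33, the stated figure.
- Keeping SD 20, 33 clusters of five detect about 8.7 mm Hg at 80% power (normal approximation), not 2.0.

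**Step 6: the same requirement at m = 2, before any uptake allowance.**
- SD 20: 982 to 983 households per arm.
- Variance 20: 50 to 51 households per arm.

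**Step 7: what 103 households × 2 per arm deliver at SD 20.**
- Standard error of the difference = √(2 × 400 × 1.25/206) = 2.20 mm Hg.
- Detectable difference at 80% power = 2.802 × 2.20 ≈ 6.2 mm Hg.
- Power for 2.0 mm Hg = Φ(2.0/2.20 − 1.96) ≈ 15% (14% with t).
- With baseline adjustment, variance × (1 − r²): the protocol gives no r. For an assumed r of 0.5 to 0.8, power is about 18% to 33%.
- If 20 is the variance, power is about 98%.

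**The case against.** Several points on the other side are fair.

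- **618 does come from stated inputs.** 33 × 5 × 1.25 × 3 reaches it. The fault is an invalid inflation step, so the number is not arbitrary.
- **The 42-adult gap matters little by itself.** With two adults per household and SD 20, power is about 14.6% with 618 and 15.3% with 660. Since 660 might be an uninflated figure on some other basis, 660 − 618 is not a proven shortfall.
- **The cluster-size mismatch is favourable.** 103 households per arm exceeds 33. At an equal 165 adults per arm, the effective number rises from 165/2.0 = 82.5 to 165/1.25 = 132, a factor of 1.6.
- **618 may not be the number analysed.** 362 households are randomised, or 724 adults at two each, and the Eligibility criteria section keeps in their arm those whom renal screening bars from the intervention.
- **The detectable-difference table was not available in the text reviewed.** It may include clusters of two or clarify the calculator inputs. It could not make the prose totals 495, 660 and 618 agree.

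A reader might infer that 80% uptake was really used, because 165/0.80 is also 206.25. The document nowhere mentions 80% uptake, and the parallel CKD step points to addition of the shortfall. A reader might also apply intention-to-treat dilution and conclude that 165/0.75² ≈ 293 per arm were needed. That is not established, because the 2.0 mm Hg was extrapolated from trials that already had 74.3 to 94.1% uptake.

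**Conclusion.** The concern stands as an inconsistency and an arithmetic error. 660 is not 33 × 5 × 3. The uptake and CKD allowances are both computed by addition where division is needed (206 for 220; 362 for 374). The 33-cluster figure belongs to a design with five adults per household, which this trial does not use.

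These slips do not by themselves show that the trial is too small. The gap between the totals is minor and the cluster-size error runs in the trial's favour. What decides the power is whether 20 is an SD or a variance: about 15% for 2.0 mm Hg in the first case, about 98% in the second. The protocol calls its planning value an SD, and on that reading, correcting 206 to 220 would not restore 80% power.

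These figures assume two-sided testing at 0.05, ICC 0.25, 103 households of two per arm, no baseline adjustment and no loss of participants.

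**What to change.** Rewrite Sample size and Recruitment as one chain for the design that is run:

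1. Use two adults per household, ICC 0.25 and design effect 1.25, and state the sidedness.
2. Reconcile the SD of 20.0 with the 33 clusters and with the description of earlier trials' spread as a variance. State which quantity was entered in the calculator.
3. Allow for uptake at most once. Under intention-to-treat it belongs on the effect; if 2.0 mm Hg already reflects trials with 74.3 to 94.1% uptake, no further allowance is needed.
4. For any exclusion allowance, divide by (1 − d).
5. Remove 660 or correct it. Keep 75% as the stated uptake input if an allowance is retained.
6. State the power or detectable difference that 309 households deliver. If a gain from baseline adjustment is claimed, give the assumed correlation.

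The cost is text and figures. No added enrolment is required, provided the delivered precision is restated honestly.

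### The inflation from 309 to 362 households multiplies by 1.173 where it should divide by 0.827, and takes a rate among people as the loss rate for whole households

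*Protocol article*

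**What the plan says.** The Recruitment section sets "a final sample size of 206 participants per study arm, leading to a total study recruitment requirement of 618 subjects". At two participants per household this is 309 households, or 103 per arm. It then says that "the systematic random sample of 309 households will be further inflated by the current CKD prevalence of 17.3% in Bangladesh" and that "the resulting 362 households will then undergo the randomization process". The reason given is kidney disease: "We will plan to exclude the households with CKD or nephrotic syndrome cases", and to that end "we will perform serum creatinine tests among the adults and urine dipstick tests among those under 18 years of age". Households with diagnosed kidney disease are already removed when the sampling frame is listed, and each listed household must have at least two adults willing to take part.

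Two other sections bear on the same step and do not match it.

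- **Eligibility criteria.** This section says that "all adults residing in the selected households initially screened for intervention will undergo serum creatinine testing". Adults below the eGFR limit are withheld from the intervention but stay in their arm under intention to treat. A household with a minor who has confirmed proteinuria is withheld from the salt but still followed in its arm.
- **Plans for collection, laboratory evaluation, and storage of biological specimens.** This section places both the blood and the urine tests in households that receive salt, once, before the intervention starts.

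**The concern.** An inflation for exclusions should leave the required number after the exclusions are made. Multiplying by one plus the loss rate does not do this; dividing by one minus the loss rate does.

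The loss rate itself is also in doubt. A national prevalence is the chance that one person is affected. Where a single case among several tested people removes the household, the chance of losing a household is higher than the per-person chance, unless cases cluster completely within households.

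What is at stake is whether the 309 households that the trial reports as its size would remain and, above all, how many households in the low-sodium salt substitute (LSSS) arm would receive salt. That arm carries two of the three planned comparisons.

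**Working it through.** **Inputs.** From Recruitment: 309 households (618/2), 103 per arm, rate 17.3%, 362 randomised, at least two adults per household. From Sample size: hypothesised effect 2.0 mm Hg.

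**Reproducing the plan's figure.** 309 x (1 + 0.173) = 362.46, which gives 362. Division gives 309/(1 - 0.173) = 373.6, or 374, which does not reproduce 362.

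**What 362 leaves if 17.3% is the household loss rate.** 362 x 0.827 = 299.4, about 10 short of 309. The loss at which 362 leaves exactly 309 is 1 - 309/362 = 14.6%, below the plan's own rate. The formula slip alone is 374 - 362 = 12 households.

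**Per-person rate against household exclusion.** With *m* tested adults, any-case exclusion and independence within the household, the loss is 1 - (1 - p)^m. For p = 0.173 and m = 2:

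- loss = 1 - 0.827² = 31.6%
- remaining, if all arms are tested = 362 x 0.684 = 248
- needed to keep 309 = 309/0.684 = 452

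With complete clustering of cases within households, the loss returns to 17.3%, so at that per-person rate the two-adult range is 17.3% to 31.6% for any degree of positive clustering.

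**The rate at which 362 would suffice.** Solving (1 - p)² = 309/362 gives p = 1 - √0.8536 = 7.6% newly found cases per person. The protocol gives no figure for newly found cases.

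**If only the salt arm is tested.** Each arm has 362/3 = 120.7 households, and the two untested arms together keep 241.3.

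| Household loss | LSSS arm left (103 needed) | Total left (309 needed) |
|---|---|---|
| 17.3% | 120.7 x 0.827 = 99.8 | 341 |
| 31.6% | 120.7 x 0.684 = 82.5 | 324 |

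**If affected households stay in their arm.** All 362 are analysed and nothing has to be replaced. Assume that an affected household gets no salt and that salt is the whole source of the effect. A 2.0 mm Hg effect then becomes 2.0 x 0.827 = 1.65, or 2.0 x 0.684 = 1.37 mm Hg, in the LSSS-arm contrasts. The comparison of control with education alone is untouched.

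**The case against.** The strongest reply is that the shortfall depends on how the sections are read together. If only salt-recipient households are tested, the total stays above 309 in both cases above. If affected households are kept under intention to treat, the analysed number is 362, more than the trial needs. Both points stand. A reader might infer from the Recruitment section alone that 362 cannot leave 309 under any reading; the documents do not support that.

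A second reply concerns the rate. Diagnosed cases are removed first, and the adult test detects only a low eGFR. The protocol does not say how the 17.3% was defined. The rate of new findings should therefore be below 17.3% per person, and it is too strong to say that household loss must be far above 17.3%. This also stands. It does not rescue 362 as derived, because the plan itself applies the full 17.3% after that removal.

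A reader might go further and take "an expected cluster membership of five adults per cluster" from the Sample size section as the number tested. With independence, loss would then be 1 - 0.827⁵ = 61.3%, leaving 140 of 362. That five is the cluster size in the power calculation, whereas the trial enrols two adults per household, so the figure can serve only as an extreme scenario. The dilution it would imply also assumes no effect in households without salt, yet the LSSS arm receives the education as well and nothing says that affected households lose it.

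Finally, the Eligibility criteria section withholds the intervention from affected adults as individuals and states a household rule only for proteinuria in minors. Any-case household exclusion is therefore the Recruitment section's rule, not one the whole protocol applies consistently.

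**Conclusion.** The formula error is certain and small: 362 should be 374 if 17.3% of households are lost, and 362 as stated leaves about 299. The unit mismatch is also plain from the text, but its size is conditional. It runs from no shortfall, at about 7.6% newly found cases per person with two adults, to about 248 households left at 17.3% per person with independence and testing in all arms.

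Under salt-arm testing the shortfall lies in that arm only, at about 100 or 83 households against 103. Under the keep-in-arm rule there is no shortfall in analysed households. The inflation then replaces nothing, and the cost is a diluted effect in the two LSSS-arm contrasts. On no reading does the stated derivation of 362 do what it is meant to do.

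**What to change.** First, reconcile the Recruitment section, the Eligibility criteria and the specimen-collection section on two questions: which arms are tested, and whether exclusion means leaving the trial or only not receiving salt. Which rule applies is for the investigators to settle.

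Then restate the number to match.

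- **If affected households leave the trial:** say that 362 yields about 299 at a 17.3% household loss, or compute the inflation as n/(1 - household rate). Give a household-level rate for newly found cases, with a range and its assumptions. If only the salt arm is tested, state the expected number in that arm.
- **If affected households stay in their arm:** report 362 as the analysed number and drop the inflation as a replacement for exclusions. State how many LSSS households are expected to receive salt and the diluted detectable effect for the LSSS contrasts, with assumptions labelled.

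The cost is a revised paragraph and aligned wording in two other sections. The stated figures become slightly less favourable.
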